#### Participants and Recruitment

We will take a census approach to recruitment in that all eligible participants in GM will be invited to participate. Identification of potential participants will take place primarily through searches of primary care practice databases to identify patients with T2D. Practice searches will be facilitated by the staff of the Greater Manchester Diabetes Clinical Research Network whenever possible. Letters from the practice, in most cases, will make initial contact with potential study participants. In some cases (according to practice preference), a text message from the practice to the patient or an email sent from the practice to the patient will be used. Posters advertising the study will be made available in practice clinics and waiting rooms.

We expect that a small number of patients with T2D will be identified through their clinical teams based in hospital outpatient clinics (most people with T2D are managed in primary care) and those attending Allied Health clinics (eg, eye screening and podiatry).

#### Inclusion and Exclusion Criteria for the Main Intervention (DMW)

The inclusion and exclusion criteria for the main intervention are presented in Textbox 2.

The goal will be to offer DMW to all 140,000 people with T2D in GM, and a clinician-facing version will be offered to all GM primary care staff. Behavioral interventions (Oviva or Changing Health) will be offered to a total of 600 patients each. MyCognition cognitive assessment will be offered to all DMW participants, and the intervention on cognitive function will be offered to the first 600 participants. Other digital interventions will be offered to DMW participants through the DMW interface as shown in Figure 1. Participants will be offered access to *additional digital interventions* through DMW.

Inclusion and exclusion criteria for the main intervention.
**Inclusion criteria**
Age ≥18 yearsType 2 diabetes (as determined by primary or secondary care records)Self-certified understanding of written EnglishRegistered with general physician in Greater Manchester
**Exclusion criteria**
Self-reported *severe mental illness not currently managed by a physician*.

**Figure 1 figure1:**
[figure not shown]
Diabetes My Way: The Main and Enabling Interventions.

#### Enrollment and Informed Consent

Enrollment to the DMW intervention will be facilitated through the website, and patients will be directed to the participant information sheet. Providing patients are aged ≥18 years and have a diagnosis of T2D, they will be able to express their interest in taking part in the study by submitting their contact details via the DMW website. Patients will register for web-based services via their general practitioner (GP) who will confirm their identity by checking their documentation. Patients are required to use these web-based service codes to register for DMW and answer a number of inclusion and exclusion criteria. Once registered (and where they match the criteria), the study consent form will be introduced. If and when completed and submitted, the patient’s account is activated, and they are enrolled in the study. When registered, but not matching the study criteria, the patient will be given access to DMW, but not entered into the study or consent process.

Enrollment to other digital interventions will also occur via the DMW website. On the basis of the inclusion and exclusion criteria, participants enrolled and using the DMW intervention will be invited to take part in additional substudies involving an additional digital intervention (Oviva or Changing Health allocated to alternate eligible participants or MyCognition). The above procedure for communicating participant information and obtaining informed consent will be repeated.

We will invite participants to enroll with either Oviva or Changing Health behavioral interventions until 600 have attended each intervention. These interventions will be offered to alternate participants enrolling with DMW, ensuring that the numbers receiving each intervention remain similar.

All DMW participants will be provided with the option of completing the MyCognition web-based cognitive assessment and will be offered the MyCognition intervention until 1000 have completed the intervention. When 1000 people have completed the intervention, DMW participants will continue to be offered the option of completing the MyCognition web-based cognitive assessment but will not be offered the MyCognition intervention. Participants will be invited to complete the MyCognition web-based cognitive assessment every 3 months during the study (a maximum of 3 times). Those completing these assessments, but without receiving the intervention, will act as a control group.

DMW study participants will be invited to access the other interventions through a notice shown at the top of the home dashboard page of the DMW. Opportunities to enroll will be available instantly upon successful log-in and acceptance of the study criteria.

#### Comparison Group

Within the short time frame available for the study, a randomized controlled trial will not be possible; therefore, the effectiveness of the interventions will be compared with groups of people choosing not to take up the offer of interventions. Data on this comparison group will be sourced from NHS Digital as part of the national GP Data for Planning and Research program. The comparison group will be sourced from patients registered in GM, the other inclusion and exclusion criteria being applied. Controls (not using the intervention) will be matched (up to 10:1) with study participants on age (+2 or −2 years), gender, ethnicity, and general practice. When appropriate, we will increase the number of controls per participant to enable additional matching on baseline levels of outcome measures, such as HbA_1c_ levels. Where there are clinically important differences between participants and controls in relation to other characteristics such as prevalent cardiovascular disease, we will include these variables as covariates regression models.

#### Outcomes

##### Overview

The primary outcomes will be intervention-related changes compared with changes observed in a matched group of controls, and the secondary outcomes will be within-person intervention-related changes (Textbox 3).

Primary and secondary outcomes.
**Diabetes My Way, Oviva, and Changing Health behavioral interventions**
Primary outcomeChange in hemoglobin A_1c_ levels [26,27].Secondary outcomesChanges in body weight or BMI, blood pressure, cholesterol, and smoking [28].Uptake, engagement, user experience, retention, completion [29], and health care use (clinic and hospital attendance and medication use).Impact of primary care staff on knowledge, skills, and confidence in diabetes management [30].Modifying effect of cognitive function [31].
**MyCognition**
Primary outcomeChange in diabetes distress score [32-34].Secondary outcomesChange in cognition scores.Changes in referral rates for traditional psychological interventions compared with controls and within-person changes.

##### User Engagement With Digital Intervention

A range of metrics will be gathered remotely with no additional burden on the participants. Measures will include the number of users offered the intervention, number of users expressing an interest in the intervention, number of active users, number of inactive users (registered but not logged onto the intervention), number of users and percentage who have viewed all learning content, number of users and of participants who have booked a coaching session (for behavioral interventions), number of coaching sessions attended, and number and percentage of participants completing digital structured education (for behavioral intervention).

### Overview of Data Items and Source of Data by Intervention in the Quantitative Study

#### Diabetes My Way

To evaluate the DMW intervention, the University of Manchester will obtain participant data from GP records via DMW, between April 1, 2016, and March 30, 2022. These data will include the following: age, sex, ethnicity, GP postcode (to assess the degree of socioeconomic deprivation) [35], diabetes type and duration, blood pressure, cholesterol, creatinine, estimated glomerular filtration rate (eGFR), smoking and body weight, height, BMI, medication, diabetes clinic attendance in primary care, and hospital visits including emergency visits.

Participant data from DMW or NHS Digital will also include ethnicity (self-provided, sometimes unreliable from primary care due to missing data), user experience or usability, service use (medication, diabetes clinic attendance in primary care, and hospital visits including emergency visits), and website activity.

Data on control participants (not using DMW) will be obtained from NHS Digital, from April 1, 2016, to March 30, 2022, and will include the following: age, sex, ethnicity, GP postcode (to assess socioeconomic deprivation), diabetes type and duration, blood pressure, cholesterol, creatinine, eGFR, smoking and body weight, height, BMI, medication, diabetes clinic attendance in primary care, and hospital visits including emergency visits.

#### Behavioral Interventions: Oviva and Changing Health

To evaluate the behavioral interventions, Oviva and Changing Health, the University of Manchester will obtain participant and control data from GP records via DMW and NHS Digital for the period April 1, 2016, to March 30, 2022, as described for DMW. Data on user experience or usability from Oviva and Changing Health participants will be transferred to the University of Manchester via DMW.

#### MyCognition

To evaluate the MyCognition intervention, the University of Manchester will obtain participant and control data from MyCognition via DMW, from GP records via DMW, and from NHS Digital for the period April 1, 2016 to March 30, 2022. Participant data transferred to the university via DMW will include cognition scores, diabetes distress scores (administered as a web-based questionnaire to participants), and usability data.

### Clinical and Biochemical Data in Study Participants

#### Overview

Clinical data collected by health care professionals during routine clinical care will enter the appropriate clinical management system (eg, GPs using the Elton Medical Information Systems health primary care electronic health record). Pseudonymization is a technique that replaces or removes all information that can be used to identify an individual. The process involves replacing names or other identifiers that are easily attributed to individuals with a study reference number. DMW will provide pseudonymized data on study participants and controls to the University of Manchester.

#### Clinical Data

The clinical data of interest includes age, sex, ethnicity, socioeconomic deprivation, diabetes type, weight, height, BMI, HbA_1c_, blood pressure level, diabetes medication, blood pressure medication, lipid lowering therapy, and service use data (attendance and nonattendance at diabetes clinics and emergency hospital visits) will be obtained from primary care records. Ethnicity will be taken from self-reported data provided at enrollment with DMW (White, South Asian, Black, mixed, or other, if *other* participants will be invited to specify using text). Socioeconomic deprivation will be assessed from the GP postcode to reduce the likelihood of participants being identified.

#### Biochemical Data

All blood sampling (eg, HbA_1c_ and serum lipids) will be conducted via routine clinical care. Participants who did not have a blood sample taken within the preceding 3-6 months will be advised through a message on the DMW website to arrange a diabetes review (weight, blood pressure, smoking status, medication review, HbA_1c_, and lipids) with their practice team at the time of enrollment in line with standard clinical care according to National Institute for Health and Care Excellence (NICE) guidance 28 [36] Participants will be advised to have repeat weight, blood pressure, medication review, and blood tests every 3-6 months in line with standard clinical care according to NICE guidance 28 [36]. Study participants will not be subject to any investigations outside of their routine care unless clinically indicated. Blood test results will be transferred to DMW from the primary care record.

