### Clinical and Biochemical Data From NHS Digital in Participants and in Controls not Providing Consent

Our study involves comparing intervention-related changes in risk factors, such as HbA_1c_ levels, in study participants with the changes occurring in a control patient cohort not receiving the intervention.

NHS Digital will use their General Practice Extraction Service (GPES) to provide GP data on all patients with T2D across GM (approximately 160,000 people) between April 1, 2016, to March 31, 2022. The core data items will include age, sex, ethnicity, GP postcode (to assess socioeconomic deprivation), diabetes type and duration, blood pressure, cholesterol, creatinine, eGFR, smoking and body weight, height, BMI, medication, diabetes clinic attendance in primary care, and hospital visits including emergency visits.

To distinguish between DMW participants and nonparticipants in the GPES data, the following steps will be taken:

DMW will supply NHS Digital with details of DMW participants including NHS numbers, GP practice with which the participant is registered, DMW generated study ID, and whether the participant is using Oviva, Changing Health, or MyCognition.NHS Digital will use NHS numbers of participants to create a DMW participant flag within the GPES data for GM. NHS numbers will then be removed.NHS Digital will supply the University of Manchester with GPES data for patients from GM with T2D.University of Manchester will store and analyze these data in accordance with NHS Digital requirements and Data Sharing Agreement.

Our study design requires that control participants be matched to participants receiving the intervention on age, sex, ethnicity, and socioeconomic deprivation (defined by GP postcode). Therefore, we require information on these 4 characteristics, in addition to the clinical and biochemical data. Socioeconomic deprivation level will be assessed from the GP postcode to minimize the risk of patients being identified. The University of Manchester will not receive any information that will enable DMW participants or control participants to be identified.

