#### Missing Data

The proposed analysis allows for missing data values. We will use clinical judgment to explore possible mechanisms of missingness, and we will consider including multiple imputation in the primary analysis, irrespective of levels of missingness, assuming a missing not at random scenario is unlikely (although multiple imputation has been found to perform better than complete case analysis, in a simple missing not at random scenario as shown) [38].

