### Note on the COVID-19 Pandemic

The plans in relation to the study participants have not been modified because of the COVID-19 pandemic. We expected digital interventions to be effective in improving self-care. However, in the context of the COVID-19 pandemic, it is clear that digital interventions could be even more valuable to people with diabetes because access to face-to-face primary care interventions for people with T2D has been extremely limited and may remain so for many months.

Before the pandemic, the study team was in contact with NHS Digital to obtain data on control participants through the Data Access Request Service. The COVID-19 pandemic provided an alternative route to obtaining these data from NHS Digital through a notice under Regulation 3 (4) of the National Health Service (Control of Patient Information Regulations) 2002. This regulation requires NHS Digital to share confidential patient information with organizations entitled to process this under Control of Patient Information Regulations for COVID-19 purposes.

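### HbA1c testing is prompted in DMW participants only, and the primary comparison uses fixed calendar dates, so completeness and timing of the outcome can differ by group

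*Protocol article*

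**What the plan says.** **Testing in participants.** Under Biochemical Data, a participant with no recent blood sample "will be advised through a message on the DMW website to arrange a diabetes review", which includes HbA1c. After that, "Participants will be advised to have repeat weight, blood pressure, medication review, and blood tests every 3-6 months". The sentence goes on: "in line with standard clinical care according to NICE guidance 28". The same section says that blood sampling "will be conducted via routine clinical care" and that "Study participants will not be subject to any investigations outside of their routine care unless clinically indicated". The Background adds that the platform sends reminders to patients and clinicians.

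**Testing in controls.** Under Comparison Group, controls are people who did not take up the offer, matched up to 10:1 on age, gender, ethnicity and general practice. Their data come from a GP record extract held by NHS Digital. The study compares participants with "changes occurring in a control patient cohort not receiving the intervention". No prompt to controls is described.

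**Comparison.** For HbA1c, the Analysis section sets baseline as April 1, 2016, to July 1, 2019, and the intervention period as July 1, 2019, to March 31, 2022. The dates are the same for everyone. Neither the matching variables nor the listed covariates include testing frequency or timing.

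**Missing data.** Multiple imputation will be considered, "assuming a missing not at random scenario is unlikely".

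**Recruitment.** The Results section reports 316 enrolled by May 10, 2021, with an extension granted.

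**The concern.** Two features combine.

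First, the intervention acts on whether and when its own primary outcome is recorded. If controls tend to be tested when their glucose control worsens, the measured control mean is too high and an inert platform looks helpful. If the controls who are tested are the engaged ones, the error reverses. Baseline adjustment removes only part of this, because the selection acts on the follow-up value. A larger control group does not reduce it.

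Second, the calendar definition ignores enrolment dates. For a late enrolee, most of the intervention period precedes any exposure. The review prompted at enrolment, which is really a baseline measurement, also falls inside that period. Controls have no counterpart to that prompted value.

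**Working it through.** **1. The plan's own figures.** Sample Size Calculations gives SD 15, difference 5, 80% power, 5% level (two-sided assumed), 86 participants and 430 controls.
- n = (1 + 1/k)(1.960 + 0.842)² × (15/5)². With k = 5 this is 1.2 × 7.849 × 9 = 84.8, so 85 participants and 425 controls. Power at 86 and 430 is 0.806, and 86/0.9 = 95.6, rounded up to 96. The figures reproduce as a 1:5 design.
- The stated ratio of 1:10 would give 78 and 780. That mismatch is a separate matter.
- The 90% behind the 96 is a planning assumption for participants. No figure is given for controls.

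**2. Is this a problem of numbers?** No. With 96 enrolled and five controls each, 30% completeness still leaves 0.3 × 480 = 144 measured controls against 86 participants. At 50% there are 240 and power is 0.756. At ten controls each and 50%, power is 0.812. The issue is bias.

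**3. Selection bias under no true effect.** Assumptions:
- baseline and follow-up HbA1c are bivariate normal, SD 15, with correlation r of 0.5 or 0.7;
- a proportion c of controls is tested;
- the odds of testing rise by OR per SD of current HbA1c;
- participant testing is unrelated to HbA1c.

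Let m be the mean standardised follow-up value among tested controls. The mean baseline among them is then r × m, so the difference left after baseline adjustment is 15 × (1 − r²) × m, that is 11.25m at r = 0.5 and 7.65m at r = 0.7. Numerical integration gives m:

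| Controls tested | OR 1.2 | OR 1.5 | OR 2.0 |
|---|---|---|---|
| 50% | 0.0904 | 0.1950 | 0.3125 |
| 70% | 0.0543 | 0.1177 | 0.1899 |
| 80% | 0.0363 | 0.0790 | 0.1288 |
| 90% | 0.0182 | 0.0399 | 0.0662 |

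The extremes at 50% are 7.65 × 0.0904 = 0.69 and 11.25 × 0.3125 = 3.52. A pooled regression with an estimated baseline slope raises the upper figures by at most about 0.1. The ranges in mmol/mol are:
- 50% tested: 0.7 to 3.6
- 70% tested: 0.4 to 2.2
- 80% tested: 0.3 to 1.5
- 90% tested: 0.1 to 0.8

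**4. If participants select in the same way.** With participants 90% tested at the same OR, m is replaced by m minus its 90% value. At 50% the range is 7.65 × (0.0904 − 0.0182) = 0.55 to 11.25 × (0.3125 − 0.0662) = 2.77. At 70% it is 0.28 to 1.39, at 80% 0.14 to 0.70, and at 90% zero.

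A second model agrees. It has threshold selection correlated ρ = 0.1 to 0.3 with the outcome, with shift ρ × 15 × φ(z)/c less its 90% value. At 50% the bracket is 0.798 − 0.195 = 0.603, giving 0.90 to 2.71. At 70% it gives 0.45 to 1.36.

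**5. Timing.** The intervention period is 33 months. Someone enrolling on May 10, 2021, has about 22 of those months before enrolment and fewer than 11 after it. As an illustration, if tests were evenly spaced and all values in the period were averaged, about two thirds of that person's values would be unexposed, which pulls a real effect towards zero. This can work against the selection bias in step 3, so the net direction cannot be stated.

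**The case against.** The strongest reply is that the prompt only repeats what standard care already recommends, and that standard applies to controls too. All tests come through routine care, none are study visits, and one value somewhere in 33 months may be enough. On that view the gap could be small, and the 80-90% rows above show how small. This stands as to size. It does not remove the asymmetry, because a recommendation is not the same as receipt, and only one group is reminded.

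Several stronger readings are tempting but are not supported:
- **Near-complete participant data against a small control set.** The 90% is an assumption, the prompt is advice, and measured controls would outnumber participants. Only a lower proportion tested is possible, and no control rate is given.
- **Control values as the self-selected ones.** Participants who act on advice select themselves too.
- **The pandemic thinned control testing.** The note says "access to face-to-face primary care interventions for people with T2D has been extremely limited", but participants use the same practices and matching is exact on practice.
- **Testing that depends on group is itself missing not at random.** Group is observed, so it is not. Only dependence on the unseen current value, given the observed data, would be.

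The Analysis section also prefers an interrupted time series where data allow, and Comparison Group permits extra matching on baseline HbA1c. Neither addresses selection on the follow-up value, and the HbA1c example is still written in calendar dates.

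Finally, windows and sensitivity analyses are often left to an analysis plan. That is fair for detail, but this article states the calendar periods and the missing-data premise, so both can be judged as written.

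**Conclusion.** The point holds in a limited form. Testing is prompted in one group only, the comparison is tied to calendar dates rather than to enrolment, and no stated safeguard covers differences in completeness or timing. The bias has unknown size and direction. On the assumed selection strengths it runs from about 0.1 mmol/mol (90% of controls tested) to 3.6 (50% tested), so it stays below the 5 mmol/mol target throughout but is not negligible at the lower testing rates. These figures rest on assumed odds ratios, correlations and control testing rates, none of which is in the article. A reader might infer that a favourable result would be an artefact of testing. The article does not support that: selection could run the other way, and counting pre-enrolment values would dilute a real effect. The change is worth making before analysis, with moderate confidence.

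**What to change.** In the Analysis section:
- Give each matched control the participant's enrolment date as index date.
- Define baseline as the last HbA1c before that date.
- Take one follow-up HbA1c per person, nearest a fixed time after the index date, within a window common to both groups that opens late enough to exclude the enrolment review.
- Choose the window with the data end of March 2022 in mind. A 12 ± 3 month window excludes anyone enrolled after about the end of June 2021 (nine months before data end) and is fully open only for those enrolled by the end of December 2020 (15 months before). A 6 ± 3 month window moves those dates to about the end of December 2021 and the end of June 2021.
- Report the proportion tested and the timing of tests by group.
- Optionally, weight by the probability of being tested given prior HbA1c and prior testing frequency. This handles selection on observed history only, not on the current value.

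In Missing Data, replace the premise that missing not at random is unlikely with a delta-adjusted sensitivity analysis for untested people in both groups. Vary delta separately by group and report where the conclusion changes. For scale, with half of controls untested, a delta of 5 mmol/mol in controls alone moves the contrast by 0.5 × 5 = 2.5.

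The cost is wording and modest programming on data already requested, with no change to the testing advice. Values outside the window are not used in the primary estimate, some late enrolees may have no value, and intervals widen slightly.
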